### 2.8. Data Analysis

The data monitoring committee will have full access to the complete final dataset. The data will be analyzed using Jamovi (Jamovi Project 2018, version 0.9.1.7, Jamovi, Sydney, Australia) and RStudio 3.15.0 software. Prior to data analysis, the Kolmogorov–Smirnov test and the Levene test will be performed to determine the normal distribution of the variables and the homogeneity of variance. For a variable to be considered as having a normal distribution, 95% of values will have to be within two standard deviations of the mean. Descriptive data will be reported as mean ± SD and range. All data will be analyzed based on the intention-to-treat principle (the last observation carried forward). If the sample is normally distributed, the Student’s *t*-test for independent samples will be used to compare the two intervention groups for the pretest, whereas ANCOVA will be used for the post-test, using the basal scores and age as covariables. Moreover, the Student’s *t*-test for related samples will be calculated to compare variables before and after the intervention in each group. If the sample is non-parametric, Kruskal–Wallis and the Mann–Whitney U tests will be used, respectively. The standardized mean differences (Cohen’s effect size) will be calculated together with the 95% confidence intervals [56]. The effect sizes (ESs) will be calculated using Cohen’s d (Hopkins). The relationship between variables will be assessed using the Pearson r correlation coefficient. If r is higher than 0.7, the determination coefficient (r^2^) will be used to determine the percentage of Y variation with regard to the X variation. Significance will be accepted at *p* ≤ 0.05.

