### 2.4. Outcomes

The primary outcome of this study will be the peak oxygen uptake (VO_2peak_) obtained in an incremental treadmill test. The secondary outcomes will be treadmill endothelial and work parameters; heart rate variability; functional parameters; relative weight and body fat distribution; quality of life; inflammatory markers; cognitive function; and exercise adherence, feasibility, and safety. The treadmill test and blood sample collection will be carried out by the cardiologist one week before and after the intervention. Data on functional performance, relative weight and body fat distribution, quality of life, and cognitive function will be recorded by the multidisciplinary group during the first and last weeks of the exercise intervention. Heart rate variability, exercise adherence, feasibility, and safety will be recorded daily during the intervention by the physical exercise graduate.

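### An ill-defined normality check chooses the analysis, and its non-parametric branch has no paired test and drops the baseline and age adjustment of VO2peak

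*Protocol article*

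**What the plan says.** Section 2.4 makes VO2peak the primary outcome. Section 2.8 then sets out the analysis in three steps.

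- **Check.** First, "the Kolmogorov–Smirnov test and the Levene test will be performed to determine the normal distribution of the variables and the homogeneity of variance". The next sentence adds a definition; for a variable to count as normal, "95% of values will have to be within two standard deviations of the mean".
- **If normal.** There are three analyses: an independent-samples t-test at pretest; at post-test, "ANCOVA will be used for the post-test, using the basal scores and age as covariables"; and within each arm a t-test for related samples "to compare variables before and after the intervention in each group".
- **If not normal.** "If the sample is non-parametric, Kruskal–Wallis and the Mann–Whitney U tests will be used, respectively".

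Nothing exempts VO2peak from this switch. The section gives no threshold for the Kolmogorov–Smirnov test and no rule for when it disagrees with the 2-SD criterion. It does not say whether the check is applied to the pooled sample or to each arm.

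**The concern.** There are three defects.

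1. **The gate.** Two criteria are named and not reconciled. The explicit one counts values within two SDs, which says little about shape. Both look at the variables themselves, whereas ANCOVA relies on roughly normal residuals.
2. **The paired comparison.** Two tests cannot be matched one-to-one with three analyses. Kruskal–Wallis and Mann–Whitney are both for independent samples, so however they are matched, before/after data would be analysed as unpaired. Hypothesis (i) in the Introduction expects improvement in both arms, so this comparison is used.
3. **The primary comparison.** Neither fallback takes covariates. If VO2peak is classed non-normal, an adjusted mean difference is replaced by an unadjusted rank comparison. The data then decide both the power and the quantity estimated.

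**Working it through.** **Inputs.** From section 2.5: 30 per arm, SD 4.75 mL/kg/min, α = 0.05 (two-sided assumed). The 30 reproduces as 1.96² × 4.75² / 1.7² = 29.99. There, 1.7 is the estimated error in a precision formula, not a treatment difference; below it serves only as an illustrative effect. The pre/post correlation r is not in the article; 0.5–0.8 is assumed. The power simulations use normal data, independent patients and baseline as the only covariate.

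**Step 1: the 2-SD rule.** At n = 30, 28/30 = 93.3% fails and 29/30 = 96.7% passes, so two values outside are enough to fail. At n = 60, 57/60 = 95% passes. Simulated share of samples classed as normal (sample mean and SD):

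| True distribution | n = 30 | n = 60 |
|---|---|---|
| Normal | 67% | 81% |
| Uniform | 98% | 99.9% |
| Two-humped | 99.8% | 100% |
| Exponential | 45% | 65% |

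Flat and two-humped data pass more often than normal data. Even in the population an exponential variable meets the rule: with mean 1 and SD 1 the share inside is 1 − e⁻³ = 95.02%.

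**Step 2: the two criteria disagree.** At n = 30 the 2-SD rule fails exponential data in 55% of samples. Kolmogorov–Smirnov with standard critical values and estimated mean and SD rejects it in 12%; with critical values corrected for the estimation, in 78%. For the two-humped case the rule fails 0.2%, against 59% and 100%. The analysis therefore depends on a choice that the plan leaves open.

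**Step 3: Mann–Whitney on pairs.** The standard error of a mean change is √(1 − r) times the one that an unpaired test assumes. At r = 0.5 the nominal cut-off of 1.96 acts like 1.96/√0.5 = 2.77, a two-sided error of about 0.6%. Simulation (n = 30, gain 1.7):

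| r | Signed-rank power | Mann–Whitney power | Mann–Whitney type I error |
|---|---|---|---|
| 0.5 | 46% | 19% | 0.7% |
| 0.7 | 66% | 15% | 0.1% |
| 0.8 | 83% | 12% | about 0% |

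**Step 4: the VO2peak comparison, if the 2-SD rule decides.** Difference 1.7, 30 per arm:

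| r | Always ANCOVA | Two-step, pooled 60 | Two-step, both arms must pass |
|---|---|---|---|
| 0.5 | 35% | 33% (−2) | 30% (−5) |
| 0.7 | 47% | 42% (−5) | 36% (−11) |
| 0.8 | 61% | 54% (−7) | 42% (−19) |

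Mann–Whitney on post-test scores alone has about 26–27% throughout. A rough check agrees. The pooled rule switches in 19% of normal samples, and 0.19 × (61 − 26) = 7 points. The per-arm rule switches in 1 − 0.67² = 55%, and 0.55 × (61 − 26) = 19 points. Repeat simulations move the ends by about a point (6–19 per arm in one). Under no difference, the two-step procedure rejected in 4.6–5.5% of trials under every reading.

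**The case against.** **The gate may be Kolmogorov–Smirnov.** The section does name it, so it cannot be said that the 2-SD rule alone decides. With Kolmogorov–Smirnov at standard critical values as the switch and normal data, simulated power equalled that of always using ANCOVA. This stands: the power losses above are conditional on the 2-SD rule deciding, and the firm defect is that two criteria are unreconciled.

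**The loss is not 35 points.** A reader might set ANCOVA at 61% against Mann–Whitney at 26% (r = 0.8) and take the gap as the cost. The plan switches only sometimes, so that gap is not its expected loss; at r = 0.5 the gap itself is only 35% against 27%.

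**Validity is intact for the primary comparison.** A reader might infer that a data-chosen test inflates false positives. The null simulations do not show this, and Mann–Whitney remains a valid comparison of two randomised groups. It is also valid for the pretest comparison.

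**Other mitigations.** Passing uniform or two-humped data to ANCOVA does no demonstrated harm at this size. Unpaired testing of positively correlated pairs is conservative: it misses effects rather than inventing them. Within-arm tests are not the primary objective. All this is fair, and limits the weight of those parts.

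**An article condenses the protocol.** That excuses omissions. Here a specific rule and specific tests are stated, and they do not fit the analyses they replace.

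**Conclusion.** The point holds as a fault in what section 2.8 states.

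- **Certain from the text:** two unreconciled normality criteria, no paired rank test, and no covariate-adjusted fallback for VO2peak.
- **Size, paired comparison:** 11–20% power against 46–83% for signed-rank, and type I error of 0–0.7% instead of 5%.
- **Size, VO2peak comparison:** about 2–7 points of power (pooled check) or about 5–19 (per-arm check), only if the 2-SD rule decides.

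These sizes rest on an illustrative effect of 1.7, SD 4.75, r of 0.5–0.8 and normal, independent data. Between-group type I error stays near 5%. The harm is to efficiency and to a stable estimand, not to the validity of the primary comparison.

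**What to change.** Rewrite a few sentences of section 2.8 before outcome data are seen:

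1. Make ANCOVA with baseline value and age the primary analysis of VO2peak, whatever any normality test shows.
2. Delete the 2-SD rule and the switch. Inspect the ANCOVA residuals instead; name a transformation or a rank-based ANCOVA with the same covariates as sensitivity analysis.
3. Name the Wilcoxon signed-rank test as the non-parametric within-group test, and report within-group changes descriptively, since neither arm is an untrained control.
4. Settle the unit of allocation. The title and the end of the Introduction describe cluster randomisation, while section 2.7 assigns participants. If allocation is by cluster, the ANCOVA must also account for clustering.

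Items 1–3 cost no patients, visits or data. If item 4 resolves to clusters, the analysis model changes as well.

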Therefore, HRV is a biomarker that can indicate the health status of the cardiovascular system, serving as an effective tool for individualizing the training load in cardiac patients. Moreover, it can be used to measure cardiovascular responses to therapeutic interventions, with HIIT-based exercise being the most recommended option. However, with the goal of obtaining improved results regarding cardiovascular rehabilitation, it is still unclear whether to opt for HIIT training or to individualize HIIT training using HRV. We hypothesize that (i) both HIIT training and HRV-guided training will improve cardiorespiratory fitness, functional performance, heart rate variability, relative weight and fat distribution, inflammatory markers, cognitive function, and quality of life in post-stroke patients but that HRV-guided training will achieve better results; and (ii) HRV-guided training will be safer and more feasible and will generate more patient adherence to the program. The primary objective of the proposed protocol is to determine the effect of HIIT- compared to HRV-guided training on cardiorespiratory fitness in post-stroke patients who undertake an 8-week cardiac rehabilitation program. The secondary aims of this trial are (i) to determine the effect of HIIT training compared to HRV-guided training on heart rate variability scores in post-stroke patients, (ii) to investigate the effect of each exercise program in terms of the adaptations obtained in functional parameters, body composition, and the quality of life of these patients, (iii) to study the effect of both programs on inflammatory markers, (iv) to determine which exercise program is more effective at improving cognitive function, and (v) to analyze whether the two exercise programs are equally feasible and safe, as well as to evaluate their effect on patient adherence to the cardiac rehabilitation program.

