### 2.2. Eligibility Criteria

To be included in the program, participants must (i) have a left ventricle ejection fraction higher than 30% after stroke and (ii) be aged between 18 and 80 years. As exclusion criteria, the following will be taken into account: (i) the presence of absolute or relative contraindications for accomplishing the treadmill test, as indicated by the Spanish Society of Cardiology; (ii) ongoing treatment for other diseases or regularly taking a drug(s) that has/have a direct or indirect effect on the nervous system (e.g., anxiolytics, antidepressants, or neuroleptics); (iii) the absence of medication to control or modify cardiovascular disease during the intervention; (iv) people who are participating or have participated in other similar exercise programs in the previous three months; and (v) inability to perform at least 80% of the workouts during the intervention.

The cardiologist from University Hospital Torrecárdenas will verify that the patients meet the inclusion criteria. The trial steering members will certify that the subjects do not meet any of the exclusion criteria. The study requirements will be explained to patients in detail verbally and via the written patient information and consent form. The model consent form is shown in Appendix A.

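### Last observation carried forward enters zero change for any patient without a post-test, which shrinks a real VO2peak difference when dropout is equal and shifts it when dropout is unequal

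*Protocol article*

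**What the plan says.** Section 2.8 (Data Analysis) sets one rule for every outcome: "All data will be analyzed based on the intention-to-treat principle (the last observation carried forward". The arms are then compared by ANCOVA on the post-test, with the baseline score and age as covariates. The article gives no other missing-data method and no sensitivity analysis.

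Section 2.4 (Outcomes) fixes what there is to carry forward:

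- Primary outcome: "The primary outcome of this study will be the peak oxygen uptake".
- Its timing, shared with the blood markers: "The treadmill test and blood sample collection will be carried out by the cardiologist one week before and after the intervention".
- Function, body measures, quality of life and cognition: "will be recorded by the multidisciplinary group during the first and last weeks of the exercise intervention".
- The exception: "Heart rate variability, exercise adherence, feasibility, and safety will be recorded daily during the intervention by the physical exercise graduate".

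The Introduction expects that "both HIIT training and HRV-guided training will improve cardiorespiratory fitness", with the larger gain under HRV guidance, and that "HRV-guided training will be safer and more feasible and will generate more patient adherence to the program". Section 2.2 lists as an exclusion criterion "inability to perform at least 80% of the workouts during the intervention".

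**The concern.** With one pre-test and one post-test, carrying the last observation forward means carrying the baseline forward. A patient who misses the post-test enters the primary analysis as someone whose fitness did not change. The investigators expect fitness to rise in both arms, so the rule removes expected gain from each arm in proportion to that arm's dropout.

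This has two consequences. If both arms lose the same share of patients, a real difference is diluted and power falls. If they lose different shares, a difference in attendance at the post-test turns into a difference in VO2peak, even where training has the same effect in both arms. The primary comparison then mixes fitness with retention, although adherence and feasibility are separate secondary outcomes.

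The rule is stated outright in the article, so it is not a detail left to an analysis plan that is not shown.

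**Working it through.** **Inputs from the protocol article.** SD 4.75 mL/kg/min, d = 1.7 and 30 patients per arm (section 2.5); one pre-test and one post-test (2.4); ANCOVA adjusted for baseline (2.8). The plan's n reproduces as a precision calculation: 1.96² × 4.75² / 1.7² = 29.99, so 30. The 1.7 is the plan's estimation error rather than a stated treatment difference, and it serves here only as a yardstick.

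**Assumptions, because the article gives no figures.** Mean gain 3 mL/kg/min; the dropout shares shown below; pre-post correlation r = 0.8; dropouts would have gained like completers.

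**Formula.** Let m be an arm's mean gain and p its share without a post-test (V = HRV-G, H = HIIT-G). Randomisation balances baseline in expectation, so under the stated rule:

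- expected difference = (1 − pV)·mV − (1 − pH)·mH
- bias = pH·mH − pV·mV

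**Equal dropout, true difference 1.7 (gains 4.7 and 3).** At 20% in both arms: 0.8 × 4.7 − 0.8 × 3 = 3.76 − 2.40 = 1.36. In simulation at r = 0.8, power is 39 to 40%, against 52% for ANCOVA on the observed post-tests.

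**Unequal dropout, no true difference (gain 3 in both arms).**

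| Dropout HIIT-G / HRV-G | False difference | Share of 1.7 | Simulated type I error, r = 0.8 |
|---|---|---|---|
| 15% / 10% | 3 × 0.05 = 0.15 | 9% | 5.7% |
| 20% / 10% | 3 × 0.10 = 0.30 | 18% | 6.4 to 6.8% |
| 25% / 10% | 3 × 0.15 = 0.45 | 26% | 8.8 to 9.8% |

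The simulations used 30 patients per arm, SD 4.75 and ANCOVA on baseline only (age omitted), with 6,000 to 8,000 trials per scenario where the number of trials is on record. Fixing the number of dropouts exactly, instead of drawing dropout patient by patient, gives somewhat lower rates: 5.1 to 5.5% at 20%/10%, with r = 0.7 and 0.85. In these null scenarios, ANCOVA on observed post-tests, with dropout unrelated to outcome, had a mean difference near zero and a type I error near 5%.

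**Direction.** Reversed dropout reverses the sign. At 10% in HIIT-G and 30% in HRV-G, the false difference is 3 × (0.10 − 0.30) = −0.60, and a true 1.7 becomes 0.7 × 4.7 − 0.9 × 3 = 3.29 − 2.70 = 0.59.

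**If dropouts gain less than completers.** If they gain a fraction k of the completers' gain, the bias is multiplied by k. At 25%/10%, k = 0.5 gives 0.5 × 0.45 = 0.225, and k = 0 gives no bias.

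**The case against.** Several stronger readings are tempting, and the article does not support them.

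- **That the trial itself predicts unequal dropout.** It predicts better adherence, and section 2.4.8 defines adherence as sessions completed. A patient can miss sessions and still attend the treadmill test, and section 2.6 encourages attendance at both tests. More loss in HIIT-G is an inference. The 80% workout criterion makes it plausible, because it ties low attendance to leaving the trial, but the article does not state it.
- **That the rule zeroes every outcome.** Heart rate variability is recorded daily, so a later value is carried there.
- **That unequal dropout always biases.** The bias vanishes if dropouts truly stay at baseline, or if dropout share times mean gain is the same in both arms.
- **That single imputation makes the standard errors too small.** Simulation does not bear this out. The average model standard error was 0.735 against an actual spread of 0.742, and type I error was 4.9% with 15% dropout in both arms. The inflation under unequal dropout comes from the shifted mean.

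It is also fair to say that the harm is modest at small imbalance: at 20%/10%, type I error stays between about 5% and 7%. What survives is the mechanism, which follows directly from sections 2.4 and 2.8, and the dilution under equal dropout, which needs no assumption about which arm loses more patients.

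**Conclusion.** The point holds for VO2peak and for every other outcome measured only at the start and end; daily heart rate variability is outside it. The stated rule enters zero change for patients without a post-test in a trial that expects both arms to improve.

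If dropouts would have gained like completers, equal dropout shrinks a real difference in proportion, by 20% of its size at 20% dropout. Unequal dropout adds a false difference equal to the gain times the dropout gap, which is 0.15 to 0.45 mL/kg/min over the range shown. If HIIT-G loses more patients, which is plausible but unstated, the bias favours HRV-G, the arm the investigators expect to do better.

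The mechanism is certain. Its size and direction depend on dropout rates, gains and a correlation that the article does not give.

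**What to change.** In section 2.8, delete the bracketed carry-forward rule and state instead that:

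1. all randomised patients are analysed in their allocated arm;
2. missing post-tests are handled under missing at random in the planned baseline- and age-adjusted comparison, either by a likelihood-based model of baseline and post-test or by multiple imputation followed by the ANCOVA, with one of the two named in advance;
3. baseline carried forward is reported only as a sensitivity analysis.

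In section 2.4 or 2.6, add that patients who stop training are asked to attend the post-test already planned. This reduces the missing data, and with it the reliance on any assumption.

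The change should be made before anyone has seen dropout by arm. It needs no extra patients and no new visit. The cost is precision: in simulation the standard error rose from about 0.74 to between 0.80 and 0.82 with ANCOVA on observed post-tests, so intervals would be roughly 8 to 11% wider (0.80/0.74 = 1.08; 0.82/0.74 = 1.11). That width reflects the information actually lost.

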This will be an 8-week, single-center, prospective, cluster-randomized controlled trial protocol in which post-stroke patients are assigned to either an HRV-based training group (HRV-G) or a HIIT training group (HIIT-G). A block randomization method will be used to randomly assign groups to interventions in equally sized sample groups. This protocol was designed in accordance with the Standard Protocol Items: Recommendations for Interventional Trials (SPIRIT) Statement [32]. To describe the intervention, the TIDieR (Template for Intervention Description and Replication) checklist by Hoffmann et al. (2014) [33] was used.

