### 2.5. Sample Size and Power

Based on the mean standard deviation established for the VO_2peak_ in a previous study by Moholdt et al. (2009) [55] (SD = 4.75 mL/kg/min) and an estimated error (*d*) of 1.7, a valid sample size providing a 95% confidence interval (CI) comprise 30 patients in each group (*n* = *CI*^2^ × *d*^2^/*SD*^2^). Therefore, a final sample size of 30 for each group (a total sample size of 60 patients) will provide a power of 97% if between and within a variance of 1. Calculations to establish the sample size will be performed using RStudio 3.15.0 software (RStudio, Boston, MA, USA). The significance level will be set at *p* ≤ 0.05.

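### The hypothesis that both programmes improve outcomes is tested only by within-arm paired tests; with no untrained arm, a significant change could be declared a training effect when it is not

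*Protocol article*

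**What the plan says.** Hypothesis (i), in the Introduction of the protocol article, has two parts. The first is that "both HIIT training and HRV-guided training will improve cardiorespiratory fitness, functional performance, heart rate variability" and a further list of outcomes. The second is the comparative part, "but that HRV-guided training will achieve better results". The primary objective is comparative as well: "to determine the effect of HIIT- compared to HRV-guided training on cardiorespiratory fitness".

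The last paragraph of the Introduction gives the design: "post-stroke patients are assigned to either an HRV-based training group (HRV-G) or a HIIT training group (HIIT-G"). Both arms receive an exercise programme, and no untrained or usual-care arm is described.

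Section 2.8 (Data Analysis) plans two kinds of test on post-intervention data. Between arms, "whereas ANCOVA will be used for the post-test, using the basal scores and age as covariables". Within arms, a t-test "for related samples will be calculated to compare variables before and after the intervention in each group". The section ends with one threshold for all tests: "Significance will be accepted at" p ≤ 0.05. It treats descriptive output separately (mean, SD and range) and does not list the paired tests there. It gives no caution about what a within-arm change can show.

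**The concern.** A before–after change in a trained arm combines the effect of training with everything else that changes over the same weeks. The protocol itself describes possible sources of such change:

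- The patients are in rehabilitation after a stroke (section 2.1), so some recovery over an 8-week programme is plausible without any effect of training.
- The functional and cognitive tests (sections 2.4.3 and 2.4.7) are taken in the first week and repeated in the last (section 2.4), so practice can raise the second score.

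Randomisation balances these influences between the arms but does not remove them from either arm. The ANCOVA contrast cancels a shift that both arms share; the paired test counts it as improvement.

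At stake is a claim that each programme works. The first part of hypothesis (i) leads towards that claim, and secondary aims (ii) and (iii) also speak of the effect of each or both programmes. The design supports only a statement about one programme relative to the other.

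**Working it through.** **Inputs from the protocol article.** 30 patients per arm and an SD of VO2peak of 4.75 mL/kg/min (section 2.5); significance at p ≤ 0.05 (section 2.8), taken here as two-sided because sidedness is not stated.

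**Inputs assumed.** The non-training change and the pre–post correlation r. The document gives neither, so ranges are shown. Patients are treated as independent.

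**The plan's own figure.** Section 2.5 uses "SD = 4.75 mL/kg/min) and an estimated error" of 1.7. Then 1.96² × 4.75² / 1.7² = 29.99, which rounds to the stated 30 per arm.

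**Step 1: shift in units of the SD of the change score.** For a paired t-test with n = 30, df = 29 and the critical value is 2.045. With no training effect and a standardised non-training change dz, the noncentrality is dz × √30.

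- dz = 0.3: 0.3 × 5.477 = 1.64, giving a 35.5% chance of significance.
- dz = 0.5: 0.5 × 5.477 = 2.74, giving 75.4%.

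**Step 2: shift in mL/kg/min for VO2peak.** With equal SDs before and after, the SD of change is 4.75 × √(2(1 − r)), and the noncentrality is shift × √30 / SD of change. The table gives the chance of a significant improvement when training has no effect. The both-arms figure is the square of the one-arm figure.

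| r (assumed) | SD of change | Shift 1.0: one arm | Shift 1.0: both arms | Shift 1.7: one arm | Shift 1.7: both arms |
|---|---|---|---|---|---|
| 0.5 | 4.75 | 20% | 4% | 47% | 23% |
| 0.7 | 3.68 | 30% | 9% | 69% | 47% |
| 0.8 | 3.00 | 42% | 18% | 85% | 72% |
| 0.9 | 2.12 | 70% | 49% | 99% | 98% |

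Example for r = 0.9 and shift 1.0: 1.0 × 5.477 / 2.124 = 2.58, giving 70%. The shift of 1.7 borrows the size of the error term in section 2.5 for scale only; the protocol does not call it a non-training change.

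**Step 3: the between-arm test under the same conditions.** Trials were simulated with the same shift (0, 1.0 or 1.7) in both arms, no training effect, and r of 0.7, 0.8 or 0.9, with 6,000 runs per setting. The ANCOVA adjusted for baseline; age was not simulated. It rejected in 4.7% to 5.3% of runs. The paired test rejected in about 5% per arm with no shift, and agreed with the table otherwise.

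**The case against.** The strongest reply is that the randomised comparison carries the trial. Section 2.8 names the ANCOVA first and adds the paired tests as a supplement; the primary objective is comparative; and the Conclusions state the expected result as one arm against the other. All of this stands, and it confines the point to a secondary inference.

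It is also fair that no passage says a significant paired test will be attributed to training, so the risk is that it could be, not that it will be. The size cannot be fixed either: time since stroke is not given, and the non-training shift and the correlation are assumed. Practice is an argument about the functional and cognitive tests; for VO2peak the case rests mainly on recovery.

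Section 2.8 also plans standardised mean differences with 95% confidence intervals, without saying whether they are within or between arms. Some of the descriptive reporting may therefore be planned already. The paired tests remain the only stated significance tests of improvement in each arm.

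Two stronger readings are tempting, and the document does not support them:

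- **Regression to the mean.** A reader might add it as a further mechanism. Section 2.2 does not select patients on an extreme value of any outcome, so it has little support here.
- **Significance in one arm but not the other.** A reader might infer that the arms will be compared through their paired p-values. With equal change in both arms, such a split would occur with probability 2p(1 − p), which is 46% at 0.3 SD and 37% at 0.5 SD. But no passage proposes that comparison, and the ANCOVA is there to make it properly.

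**Conclusion.** The point holds for the first part of hypothesis (i). Improvement under each programme is hypothesised, tested within each arm at p ≤ 0.05, and cannot be separated from recovery or practice in a design where everyone trains. On the assumed ranges, the chance of a significant paired test without any training effect runs from 36% to 75% (0.3 to 0.5 SD of change), or from 20% to 70% for VO2peak (shift 1.0 mL/kg/min, correlation 0.5 to 0.9). These figures show how readily a modest shift becomes significant; they do not estimate the shift in this population.

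A reader might infer that the main result is compromised. It is not: a non-training shift common to both arms leaves the ANCOVA at about its nominal 5%. The plan should be changed on this point because it invites a claim that the design cannot support and the correction is cheap.

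**What to change.** In section 2.8, replace the paired significance tests with the within-arm mean change and its 95% CI, labelled descriptive. State that every claim of effect rests on the baseline-adjusted between-arm ANCOVA difference.

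In hypothesis (i), state that improvement in both arms describes change over time and cannot be attributed to training without an untrained control. This sentence matters most: a within-arm 95% CI that excludes zero gives the same answer as the paired test, so removing the p-value alone does not settle attribution.

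The cost is wording only, with no added patients, visits or data. The downside is that one claim becomes less favourable.

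### The arms are compared by ANCOVA, but the only effect estimate and 95% CI named is Cohen's d, so no adjusted VO2peak difference in mL/kg/min is planned

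*Protocol article*

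**What the plan says.** Section 2.4 of the protocol article fixes the endpoint: "The primary outcome of this study will be the peak oxygen uptake". Section 2.8 sets the between-arm test after the intervention, for data judged normal: "ANCOVA will be used for the post-test, using the basal scores and age as covariables".

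For the size of the effect, section 2.8 states: "The standardized mean differences (Cohen’s effect size) will be calculated together with the 95% confidence intervals". The next sentence confirms that effect sizes will be Cohen's d. Natural units appear in that section only in the descriptive summary: "Descriptive data will be reported as mean ± SD and range".

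Section 2.5 plans on the natural scale. It uses "SD = 4.75 mL/kg/min" and "an estimated error (*d*) of 1.7" to arrive at "30 patients in each group".

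The article does not say whether raw means, adjusted means or changes enter d, which SD divides it, or whether it describes the difference between arms or the change within an arm (paired t-tests are planned in the same paragraph).

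**The concern.** The p-value for the main comparison comes from a model that adjusts for baseline and age. The only named estimate with an interval is a standardised difference that, by its usual definition, comes from no such model. Three things follow.

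- **Units.** The reader gets no interval in mL/kg/min for VO2peak, the scale on which the trial was sized and on which a change in fitness can be judged.
- **Coherence.** A test and an interval from two different analyses can point in different directions.
- **Dependence on the sample.** Dividing by an observed SD ties the effect partly to how varied the enrolled patients are, and section 2.2 admits ages 18 to 80.

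Because the definition of d is left open, the choice of its numerator and denominator could also be made after the data are seen.

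**Working it through.** **Inputs.** From section 2.5: SD 4.75 mL/kg/min, estimated error 1.7, 30 per arm. From section 2.8: ANCOVA on baseline and age, significance at 0.05 (two-sided assumed). Not in the documents, so assumed and varied: the correlation r between baseline and post-test VO2peak.

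**The plan's own figures.** The precision formula for one mean gives n = 1.96² × 4.75² / 1.7² = 29.99, so 30 per arm. The 1.7 is therefore a margin of error in mL/kg/min, not a treatment effect. The stated 97% power is reproduced for a difference of 1 SD with 30 per arm (0.972 by the normal approximation, 0.968 by the noncentral t).

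**Interval width, unadjusted.** SE = 4.75 × √(2/30) = 1.226. Half-width = 2.002 × 1.226 = 2.45 mL/kg/min.

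**Interval width, ANCOVA.** SE = 1.226 × √(1 − r²), with 56 degrees of freedom (t = 2.003):

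| r | ANCOVA half-width (mL/kg/min) | Unadjusted half-width (mL/kg/min) |
|---|---|---|
| 0 | 2.46 | 2.45 |
| 0.5 | 2.13 | 2.45 |
| 0.7 | 1.75 | 2.45 |
| 0.8 | 1.47 | 2.45 |

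**One worked case.** Take r = 0.8 and suppose that the raw and adjusted differences are both 1.7.

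- ANCOVA: SE = 1.226 × 0.6 = 0.736, t = 1.7/0.736 = 2.31, p about 0.025.
- Cohen's d = 1.7/4.75 = 0.358, SE = √(2/30 + 0.358²/120) = 0.260, 95% CI = 0.358 ± 1.96 × 0.260, or −0.15 to 0.87.

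The test is significant and the reported interval includes zero.

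**How often the two disagree.** The simulation used 6,000 trials per setting, normal data, 30 per arm and SD 4.75, with age included in the model but unrelated to outcome. It compared ANCOVA p ≤ 0.05 with whether the conventional d interval excludes zero. Percentage of trials in disagreement:

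| True difference (mL/kg/min) | r = 0 | r = 0.5 | r = 0.7 | r = 0.8 |
|---|---|---|---|---|
| 0 | 1.4 | 4.7 | 7.0 | 8.0 |
| 1.7 (illustrative) | 5.0 | 16.0 | 28.1 | 40.4 |
| 2.5 (illustrative) | 5.5 | 19.2 | 30.8 | 40.7 |
| 4.75 (1 SD) | 1.4 | 2.6 | 3.4 | 3.2 |

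At r = 0.7 and a difference of 1.7, 22.6% of trials have a significant ANCOVA with a d interval that includes zero, and 5.5% the reverse.

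**The case against.** The strongest reply is that the article never says d is unadjusted. It could be formed from ANCOVA-adjusted means, and the method it cites for the interval is not available here. This stands: a reader might infer that the plan fixes an unadjusted interval, but that follows only from the usual definition of d. The width and disagreement figures hold only under that definition.

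A reader might also infer that the interval is wrong or always too wide. The documents do not support this. In a randomised comparison of independent patients, an unadjusted interval keeps its nominal coverage and is merely less precise. How much less depends on a correlation the article does not give, and at r = 0 nothing is lost.

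It is also fair to say that 1.7 is a precision figure. Using it as a true difference is an illustration, and at the 1 SD difference that matches the stated power, disagreement is rare. Descriptive means will let a reader recover a raw difference in mL/kg/min, though not the adjusted one or its interval.

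Finally, details of an ANCOVA contrast are often left to an analysis plan, and the article does not say that nothing else will be reported. This carries less weight, because the article is not silent on the effect measure: it names one, and that measure is not the model's own contrast. Even a d built from adjusted means would leave the primary result without an interval in mL/kg/min.

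**Conclusion.** The point holds in limited form. Section 2.8 tests the arms by ANCOVA but names only a unitless Cohen's d as the effect estimate with a 95% CI. The lack of a planned adjusted difference in mL/kg/min does not depend on r or on how d is computed.

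The rest is conditional on d being the conventional raw difference over the pooled SD. Then the ANCOVA interval is narrower by about 13%, 29% or 40% at r of 0.5, 0.7 or 0.8 (1 − 2.13/2.45, 1 − 1.75/2.45, 1 − 1.47/2.45). Test and interval would disagree in about 16%, 28% or 40% of trials at a true difference of 1.7, and in about 1–3% at 1 SD.

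These figures also assume independent patients. The article calls the trial cluster-randomised, while section 2.7 allocates participants. Any real clustering would change both intervals and is a separate matter.

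This should be changed, but it is a poor choice of effect measure and not a demonstrated error in the test.

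**What to change.** In section 2.8, name the ANCOVA-adjusted between-arm difference in post-test VO2peak, in mL/kg/min, with its 95% CI from the same model, as the primary estimate. Do the same in native units for the continuous secondary outcomes analysed by ANCOVA. This does not extend to adherence, feasibility or adverse-event counts, for which an adjusted mean difference is not the natural summary.

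If Cohen's d is kept, report it as supplementary. State that its numerator is the adjusted difference and which SD divides it. Any sample SD still carries the dependence on case mix, which is a reason not to make d the main result.

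The cost is one or two sentences. No new data, extra analysis model or change in sample size is needed.
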